### Sample-size

The expected variations in the research outcome variable determines the sample size for the study;

n=2Z1−α2+Z1−β2σ2/d2
 (where n is the sample size per group,

Z1−α2
= 1.96 at α = 0.05,

$Z_{1-\beta }$
 = 0.84 (power at 80% power), σ = standard deviation of the primary outcome variable stress level of the mother as measured by serum cortisol level = 2.58 μg/dl (
Stjernholm, Nyberg, Cardell, & Höybye, 2016), d = clinically significant difference = 0.55 μg/dl. The sample size, calculated with an anticipatory attrition rate of 10%, is 768.

### Recruitment and consent

All the low-risk primigravid women at or after 37 weeks of gestation attending the outpatient services at tertiary care hospitals for an antenatal check-up will be oriented about the implementation of peanut ball during labor by using the peanut ball positions chart prepared by
premier birth tools and by showing the video on peanut ball during labor prepared by the researcher.

Thereafter, the mothers will be screened in the labor room based on the inclusion criteria. The research team will explain the research purpose and procedure to the eligible mothers and, if they are willing to participate, informed written consent will be taken.

### Participant allocation/randomisation

Subsequently, the low risk primigravid women at 2–3 cm of cervical dilatation preferring a vaginal delivery will be block randomised to peanut ball intervention group or standard care control group by an external member (labor room nurse) with the help of SNOSEs. The research assistant and research nurse carrying out data collection, data entry, and data analysis will be blinded to group allocation.

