**Figure 2. f2:**
[figure not shown]
Different sizes of peanut balls.

Adherence to intervention protocols and procedures will be done continuously by research assistants throughout the intervention by being with the patient and educating and comforting the mother.

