### Outcome measures

Maternal and neonatal outcomes will be measured by the research assistants at different points of time and compared between the intervention and control groups. The maternal outcome includes measurement of the duration of the active stage of labor, duration/pushing effort in the second stage of labor, mode of delivery, the need of pain medications, perception of pain, behavioural response during the active stage of labor, serum analysis of cortisol level, the proportion of postpartum hemorrhage, and neonatal outcome includes a pattern of fetal heart rate, APGAR score (Apgar V, 1958), birth injuries, and salivary cortisol level.

During the active stage of labor blood samples will be collected twice from the mothers in both groups for serum cortisol analysis. The 1
^st^ sample will be collected when cervical dilatation is 3–4 cm and the 2
^nd^ sample will be collected after full dilatation of the cervix and these will be sent to lab for analysis. An umbilical cord blood sample will be collected from the newborn at the time of birth to check the serum cortisol level, and salivary cortisol will be collected from the newborn within one hour of birth to check the salivary cortisol level. An observational record on the progress of the labor will be done for both the groups once they reach 4 cm of cervical dilatation by using the
WHO partograph Both the groups will be observed for their behavioral responses for any two hours during the first stage of the labor with the cervical dilatation ranging from 4–7 cms by using the behavioral response observational checklist (Karkada
*et al.*, 2010) Both the neonatal and maternal outcomes will be recorded by using the outcome of the labor assessment tool (
[name], 2022f) and WHO Partograph, and during postnatal period before getting discharged from the hospital, ie., 3–4 days after the delivery, women from both of the groups will be assessed for their childbirth experience by using a questionnaire for assessing the childbirth experience (QACE) tool (
Carquillat, P. *et al.*, 2017). Maternal satisfaction regarding assistance provided during labor/delivery will be measured by using VAS (visual analogue scale) patient satisfaction score (
Hayes and Patterson, 1921).

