For the study the participant recruitment began in the month February 2020. To date, we have enrolled and randomised 550 low-risk primigravid mothers. Out of the total, 225 mothers were recruited to the intervention and 225 mothers were recruited for the control group. Mothers’ unacceptance to utilise the peanut ball during labor is a challenge faced during the initial part of the study. To encounter this, all the primigravid women at or after 37 weeks of gestation attending antenatal outpatient units were given informational material about the “Peanut ball use during labor”. This educational material has oriented and familiarised the mothers with peanut ball and its uses during labor which ultimately increased the rate of peanut ball acceptance and use during labor.

Along with that, coronavirus disease 2019 (COVID-19) imposed a lockdown, and after that, institutional restrictions to resume research activities to mitigate new cases of infection had made the study come to a halt. Recruitment for the study was stopped, and we lost participants for around five months. Due to this situation, we have fallen behind the recruitment timeline. To combat this, we utilised this duration to initiate a systematic review that will bring new evidence to implement peanut ball during labor.

Besides these challenges, there are two possible limitations in this study, first, ascertainment bias, as the investigators are aware of the intervention the participants are receiving. In this project, the investigator and participants will know the allocation group for the women, as the woman will either utilise the peanut-ball or not, so they cannot be blinded. The strategy implemented to reduce the ascertainment bias is allocation concealment using SNOSEs by the labor room senior nurse on duty. The research assistant and research nurse carrying out data collection, data entry, and data analysis will be blinded to group allocation. The second limitation is compliance with the intervention during labor. To tackle this, a trained nurse will be present throughout the labor process and encourage and motivates the mothers to use the peanut ball continuously.

Despite these possible limitations, this novel approach will be a promising intervention to promote labor progress and prevent unnecessary caesarean section and instrumental birth during the second stage of labor.

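### Staff who collect outcomes are declared blinded, yet they sit with women using a visible ball; staff-observed in-labour outcomes, chiefly the behaviour checklist, are open-label

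*Protocol article*

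**What the plan says.** Under Participant allocation/randomisation the article states: "The research assistant and research nurse carrying out data collection, data entry, and data analysis will be blinded to group allocation". The Discussion repeats this.

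Three other places describe what these staff do.

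- In the paragraph after Figure 2, in the Intervention part: "Adherence to intervention protocols and procedures will be done continuously by research assistants throughout the intervention by being with the patient", with education and comfort given at the same time.
- Under Outcome measures: "Maternal and neonatal outcomes will be measured by the research assistants at different points of time".
- Also under Outcome measures, for the behaviour checklist, which is scored between 4 and 7 cm: "Both the groups will be observed for their behavioral responses for any two hours during the first stage of the labor".

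The Intervention section has the ball positions start at 4 cm or later and continue until the woman is ready to push. The Discussion accepts that the investigator and the women cannot be blinded, because ball use is visible, and names ascertainment bias as a limitation. Its answer is: "The strategy implemented to reduce the ascertainment bias is allocation concealment using SNOSEs".

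**The concern.** The same staff role is described as blind, as sitting with the woman while she uses a visible device, and as measuring her outcomes. These cannot all be true for anything observed at the bedside.

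The outcome most exposed is behavioural response. It has its own hypothesis (H2), the abstract lists it among the primary outcomes, and it is a 50-item checklist filled in by an observer. If the text stands, a judgement made with the arm known would be reported as blinded.

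Two further features make this worse. The safeguard named against ascertainment bias acts before assignment and cannot affect scoring afterwards. And the two hours of observation are not fixed, so a calmer or harder stretch of labour could be picked differently in the two arms.

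**Working it through.** **Setting the sections side by side**

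1. *Who is called blind:* the research assistant and research nurse who collect, enter and analyse data (Participant allocation/randomisation; Discussion).
2. *Who is at the bedside:* research assistants, continuously during the intervention (paragraph after Figure 2).
3. *Who measures outcomes:* research assistants (Outcome measures).
4. *When the ball is in use:* from 4 cm or later until pushing (Intervention).
5. *When behaviour is scored:* two hours somewhere between 4 and 7 cm (Outcome measures). This overlaps item 4.
6. *Whether the arm is visible:* yes, by the Discussion's own account, though it draws the conclusion only for the investigator and the women.

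Items 2 to 6 contradict item 1 for bedside observation. If the adherence assistants and the outcome assistants were different people, an assessor watching the woman at 4–7 cm would still see whether she has a ball.

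**Which outcomes are affected**

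- *Behaviour checklist:* exposed.
- *Stage timings, partograph readings, APGAR and other ratings:* exposed where the same staff record them.
- *Serum, cord and salivary cortisol:* laboratory assays (Serum cortisol and neonatal cortisol assessment), largely protected from observer scoring.
- *Data entry and analysis:* can be blinded if arms are coded. The research assistant also does the data entry (Data entry and storage), so a code does not blind an assistant to women she attended herself.

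Table 1 reports agreement of 0.97 for the checklist. That does not exclude bias, because raters who all see the ball can share the same bias.

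**The plan's own figure**

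Inputs from Sample-size: z = 1.96 and 0.84, SD 2.58 μg/dl, difference 0.55 μg/dl, attrition 10%.

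n per arm = 2 × (1.96 + 0.84)² × 2.58² / 0.55² = 345.03

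345.03 / 0.90 = 383.4, rounded up to 384 per arm; 2 × 384 = 768.

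This reproduces the stated 768, and the point does not change it.

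**Illustration of sensitivity to scoring bias**

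Suppose the ball has no effect on behaviour and scoring shifts one arm by b SD, with 345 evaluable per arm. b is an assumption; no document figure supports any value.

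SE of the standardised difference = √(2/345) = 0.0761

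P(p < 0.05) = Φ(b/0.0761 − 1.96) + Φ(−b/0.0761 − 1.96)

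| Assumed b (SD) | Chance of a false significant result |
|---|---|
| 0 | 0.05 |
| 0.05 | 0.10 |
| 0.10 | 0.26 |
| 0.20 | 0.75 |
| 0.30 | 0.98 |

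The observed difference that just reaches significance is 1.96 × 0.0761 = 0.149 SD. This is a two-sample approximation; Data analysis plans repeated measures ANOVA for behavioural response.

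**The case against.** The contradiction itself has no good answer in the text, but several stronger readings go too far.

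- *That nothing recorded in labour is blinded.* A reader might infer this. Both maternal cortisol samples are drawn in labour but measured on a laboratory analyser, and maternal cortisol is the outcome that sized the trial. Seeing the ball does not change that reading.
- *That the article hides the problem.* It does not. The Discussion admits ascertainment bias and says the investigator and the women are not blinded. What remains wrong is the claim for bedside collectors and the reason given for the envelopes.
- *That pain is a known observer-rated outcome.* Research objectives and Outcome measures speak of the woman's perception of pain. Only Outcome of the labor assessment tool mentions an objective assessment, and it does not say who makes it.
- *That raters choose the hours to suit the arm.* The article does not say who picks the two hours, and a condensed article may leave procedure to the full protocol. The wording permits a choice made with the arm known; it does not show that one is made.
- *That a bias of 0.149 SD is enough to make H2 significant.* That figure is a threshold for an observed difference. A systematic shift of that size would give significance about half the time, and it says nothing about how large the bias is.

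All of these objections stand as limits on scope and size. None restores the blinding claim.

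**Conclusion.** The article claims blinding that the trial cannot have for staff-observed outcomes in labour. The behaviour checklist is the main casualty; stage timings and other ratings are affected as far as the same staff record them. Laboratory cortisol is largely unaffected, and the sample size is untouched.

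The envelope rationale is wrong as written: concealment guards against selection at assignment, not against biased assessment after it. The loose two-hour period adds a possible route for bias, not a demonstrated one.

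The size of any bias is unknown. The range of about 26–75% false positives rests on an assumed shift of 0.1–0.2 SD, 345 evaluable women per arm and a simple two-group test. The contradiction does not depend on that range.

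A reader might also infer that these outcomes should be moved down to secondary. Lack of blinding does not by itself require that, and the abstract lists behavioural response and pain perception among the primary outcomes.

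**What to change.** 1. **State blinding by outcome.** Say that bedside collectors are not blinded. Claim blinding only for cortisol assay staff (coded tubes) and for the analyst and data entry where arms are coded.
2. **Delete the statement that the envelopes reduce ascertainment bias.** Report behaviour and other staff-observed outcomes as open-label, and leave their place in the outcome hierarchy unchanged on this ground.
3. **Set one start rule for the two-hour behaviour window, for women still to be enrolled.** It must be identical in both arms and must not depend on ball placement. Record the start time and the dilatation at the start. A window opened at the first examination at 4 cm or more could begin before the ball is placed, because positioning starts at 4 cm or later, so the rule needs thought before it is adopted.
4. **Report a sensitivity analysis of the behaviour score by period,** before and after the change.

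The cost is wording, tube codes and two recorded fields, with no extra staff and no change to 768. There are two downsides. The blinding statement becomes less favourable, and the behaviour score will have two measurement periods. The second matters because the Discussion reports 550 women already randomised (768 − 550 = 218 remaining), although its arm counts of 225 and 225 sum to 450, which would leave 318. The corrected blinding statement applies to all women; the window rule can govern only those still to come.

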### Intervention

The peanut ball positioning is done at or after 4 cm of dilatation by a trained nurse-midwife whenever the mother is lying or sitting on the bed. Peanut balls are available in four sizes: 40 cm, 50 cm, 60 cm, and 70 cm to fit different participants as reported by
Grant & Clutter in 2014. The researcher will make sure that the suitable size of the ball is given to the woman as recommended by the premier birth tools as per the height of the mother, that is: 40 cm for women whose height is under 5′3″, 50 cm is the most common size and exclusivly used for women with 5′3″ to 5′ 6″ height, 60 cm for women 5′7″ or taller or overweight women, and 70 cm used only to sit on and straddle on the peanut ball as reported by
Grant C in 2015. All the sizes of peanut balls will be available in the labor room (
Figure 2) to use during labor and will be covered with clean peanut ball covers. A suitable peanut ball will be provided to the mother to give four main peanut ball positions: sitting, semi-sitting, side-lying, and tuck position until the mother is ready to push during the second stage of labor.

**Figure 2. f2:**
[figure not shown]
Different sizes of peanut balls.

Adherence to intervention protocols and procedures will be done continuously by research assistants throughout the intervention by being with the patient and educating and comforting the mother.

### Standard care

The control group of women will receive the standard/routine care provided in the labor room of the tertiary care setting.

### Criteria for discontinuing from the study

Participants will be recruited only after informed written consent. Participants participation in this study is voluntary and they can withdraw their participation at any time, without giving any reasons. They will still get the usual routine care during labor, and non-participation will not have any negative consequences on their subsequent medical treatment or relationship with the treating obstetrician and midwife. If the participant withdraws from the study before data collection is completed, their data collected till the withdrawal will be used in the study report.

### Outcome measures

Maternal and neonatal outcomes will be measured by the research assistants at different points of time and compared between the intervention and control groups. The maternal outcome includes measurement of the duration of the active stage of labor, duration/pushing effort in the second stage of labor, mode of delivery, the need of pain medications, perception of pain, behavioural response during the active stage of labor, serum analysis of cortisol level, the proportion of postpartum hemorrhage, and neonatal outcome includes a pattern of fetal heart rate, APGAR score (Apgar V, 1958), birth injuries, and salivary cortisol level.

During the active stage of labor blood samples will be collected twice from the mothers in both groups for serum cortisol analysis. The 1
^st^ sample will be collected when cervical dilatation is 3–4 cm and the 2
^nd^ sample will be collected after full dilatation of the cervix and these will be sent to lab for analysis. An umbilical cord blood sample will be collected from the newborn at the time of birth to check the serum cortisol level, and salivary cortisol will be collected from the newborn within one hour of birth to check the salivary cortisol level. An observational record on the progress of the labor will be done for both the groups once they reach 4 cm of cervical dilatation by using the
WHO partograph Both the groups will be observed for their behavioral responses for any two hours during the first stage of the labor with the cervical dilatation ranging from 4–7 cms by using the behavioral response observational checklist (Karkada
*et al.*, 2010) Both the neonatal and maternal outcomes will be recorded by using the outcome of the labor assessment tool (
[name], 2022f) and WHO Partograph, and during postnatal period before getting discharged from the hospital, ie., 3–4 days after the delivery, women from both of the groups will be assessed for their childbirth experience by using a questionnaire for assessing the childbirth experience (QACE) tool (
Carquillat, P. *et al.*, 2017). Maternal satisfaction regarding assistance provided during labor/delivery will be measured by using VAS (visual analogue scale) patient satisfaction score (
Hayes and Patterson, 1921).

### Outcome of the labor assessment tool

The researcher prepared a record of the outcome of labor to document maternal and neonatal outcomes. The maternal outcome consists of 18 items, such as duration of labor, nature of delivery, need of pain medications, objective assessment of pain, evaluation of maternal and fetal cortisol levels and postpartum hemorrhage etc. The neonatal tool includes details of APGAR score at birth, weight of the newborn, neonatal injuries during birth and particulars of NICU admission etc. (
[name], 2022f).

### Serum cortisol and neonatal cortisol assessment

Blood samples will be collected twice during labor to determine the stress level. The first blood sample will be collected when cervical dilatation is 4–5 cm, and the second will be collected when cervical dilatation is of 10 cm from both groups and these will be sent to the biochemistry lab for analysis. After complete coagulation, the blood sample will be centrifuged, and then the serum will be separated for analysis of cortisol concentration. A blood sample from the umbilical cord will be taken at the time of birth to check the serum cortisol level of the baby, and saliva will be collected within one hour of birth by using swab stick by keeping it in baby’s mouth for two minutes to check the salivary cortisol level. The serum will be separated by centrifuging the cord blood. Using the principles of electrochemiluminescence immunoassays, cortisol levels will be measured in serum and cord blood using the Cobas -602 e-immunoassay analyser. Assay reagents are obtained from Roche Diagnostics. The saliva samples will be immediately frozen at 20° C until analysis. The free cortisol will be determined by ELISA.

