## Abstract

Frequent positional changes and movements during labour is one of the recommendations by the World Health Organization (WHO) to prevent prolonged labour, thereby avoiding cesarean sections. However, labour induction, continuous fetal monitoring in supine position and immobilising the women during labour are standard practices in most private hospitals. To combat these problems and to implement WHO recommendations, the peanut ball is an effective device through which frequent positional changes will be achieved without disrupting the labour procedures. The current study aims to evaluate the effectiveness of the peanut ball device during labour on maternal and neonatal outcomes and assess the stress response induced by labour in terms of maternal and neonatal cortisol in low-risk primigravid women. The study is a prospective, block randomised controlled trial with parallel arms. A total of 768 study participants will be randomised to the peanut-ball group (intervention) and standard care group (control). The intervention group will receive different peanut ball positions during labour at or after 4 cm of cervical dilatation. The primary outcomes of the study are maternal outcome that includes measurement of duration of the active and the second stage of labour, stress level as measured by serum cortisol level at 3–4 cm and at 10 cm of cervical dilatation, mode of delivery, perception of pain, behavioural response during the active stage of labour and neonatal outcomes, which includes the pattern of fetal heart rate, APGAR score, birth injuries, and umbilical serum and salivary cortisol level. The collected data will be compared between the intervention and control groups.

**Trial Registration:** This research is registered under the CTRI (Clinical Trials Registry of India) (
CTRI/2019/08/020802) (21/8/2019).

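### The first maternal cortisol sample is given two different dilatation windows, one lying wholly at or after the start of ball use, and no rule says the sample comes first

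*Protocol article*

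**What the plan says.** All references are to the Protocol article.

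- **Abstract:** the primary outcomes include "stress level as measured by serum cortisol level at 3–4 cm and at 10 cm of cervical dilatation".
- **Outcome measures:** the first "sample will be collected when cervical dilatation is 3–4 cm"; the second follows at full dilatation.
- **Serum cortisol and neonatal cortisol assessment:** "The first blood sample will be collected when cervical dilatation is 4–5 cm"; the second is at 10 cm.
- **Intervention:** "The peanut ball positioning is done at or after 4 cm of dilatation". The Abstract gives the same starting point.
- **Participant allocation/randomisation:** the envelope is used for "low risk primigravid women at 2–3 cm of cervical dilatation", so allocation precedes either sampling window.
- **Sample-size:** maternal serum cortisol is the sizing variable, with SD 2.58 μg/dl and a difference of 0.55 μg/dl.
- **Hypotheses (H3):** maternal cortisol levels differ between the groups.
- **Data analysis:** stress level is compared by repeated measures ANOVA. The decisive term is not named.

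No section orders the first blood draw relative to the first ball positioning.

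**The concern.** The two windows share only the value 4 cm. At 3–4 cm, the sample falls before the ball or, at most, at the dilatation where it may start. At 4–5 cm, the whole window lies where ball use is already allowed. Staff working from different sections would collect a mixture of the two.

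This matters because the first sample is one of the two repeated measures of the outcome on which the trial was sized. If it precedes the ball, an effect on cortisol appears in the group-by-time term. If it follows the ball, the intervention arm's first value may already carry part of the effect, while the control arm's cannot. That part moves into the group main effect and the interaction shrinks. With a mixture, neither term has one clear meaning.

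**Working it through.** **1. The plan's own sample size.** n per arm = 2(1.96 + 0.84)² × 2.58² / 0.55² = 2 × 7.84 × 6.6564 / 0.3025 = 345.03, taken as 345. Allowing 10% attrition: 345 / 0.9 = 383.3, rounded up to 384 per arm, or 768 in total. The stated figure is reproduced. The formula compares two means at a single time point, so the sampling conflict does not alter it.

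**2. The windows against the start of the ball.**

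| Source | First sample | Overlap with ball use (from 4 cm) |
|---|---|---|
| Abstract; Outcome measures | 3–4 cm | at 4 cm only |
| Cortisol assessment section | 4–5 cm | whole window |

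Ball use may begin later than 4 cm, so a 4–5 cm sample can follow it but need not.

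**3. Illustrative consequence for the change (group-by-time) contrast.** From the article: SD 2.58, difference 0.55, two-sided α 0.05, 345 analysed per arm. Assumed, because the article gives no figure: equal SD at both times, correlation r between the two samples, and f, the average share of the effect already present in the intervention arm's first sample. For example, f = 25% would arise if half of those women were sampled after ball use and each carried half of the effect (0.5 × 0.5).

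- Contrast = 0.55 × (1 − f)
- SD of change = 2.58 × √(2(1 − r)), which is 2.58 at r = 0.5
- SE at r = 0.5 = 2.58 × √(2/345) = 0.196
- Power = Φ(contrast/SE − 1.96)

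At f = 25%: 0.4125/0.196 − 1.96 = 0.14, giving 56%. At f = 50%: 0.275/0.196 − 1.96 = −0.56, giving 29%.

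| f | Contrast (μg/dl) | r = 0.3 | r = 0.5 | r = 0.7 |
|---|---|---|---|---|
| 0% | 0.55 | 66% | 80% | 95% |
| 10% | 0.495 | 57% | 71% | 90% |
| 25% | 0.41 | 43% | 56% | 77% |
| 50% | 0.275 | 22% | 29% | 44% |

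**4. The same assumptions (r = 0.5) for other contrasts.**

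- 10 cm values alone: contrast 0.55, SE 0.196, power 80% whatever f is.
- 10 cm value adjusted for the first sample: contrast 0.55 × (1 − r f), SD 2.58 × √(1 − r²) = 2.234, SE 0.170. Power is 90%, 81% and 68% at f = 0%, 25% and 50%.
- Group main effect (mean of both samples): contrast 0.55 × (1 + f)/2, SD 2.58 × √((1 + r)/2) = 2.234, SE 0.170. Power is 37%, 52% and 68% at the same f, so it rises with early effect.

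**The case against.** The strongest reply has four parts.

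- **It may be a drafting slip.** Two of the three statements agree on 3–4 cm, and practice may have followed them. This is possible, but the article does not say so, and the outlying window is in the section describing how cortisol is assessed.
- **The harm depends on the contrast.** H3 concerns levels, the sample size rests on one time point, and no change score is specified. This stands. A reader might infer that the trial's cortisol comparison drops to 56% or 29% power. The article does not support that: those figures belong to the change contrast alone, at assumed values of f and r. The 10 cm comparison keeps 80%, adjustment for the first sample loses less, and the group main effect gains.
- **The article never calls the first sample a baseline.** This also stands. It does enter the repeated measures model as the first of two measures, and that is enough for its timing to matter.
- **Sampling after allocation is not in itself an error.** A reader might infer that the draw should come before the envelope is opened. The article does not support that either: randomisation at 2–3 cm followed by sampling at 3–4 cm is coherent, and the result is a laboratory immunoassay. What matters is the order relative to ball use.

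None of this removes the contradiction or supplies the missing order.

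**Conclusion.** The contradiction holds and needs correction: 3–4 cm in two places, 4–5 cm in a third, ball use from 4 cm, and no rule that the sample precedes it. It affects a stated primary outcome, which is also the sizing variable, and it changes what the group-by-time term measures.

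The size of any bias cannot be derived from the article. The power figures show sensitivity only. At 50% of the effect already present, power for the change contrast runs from 22% to 44% for r between 0.3 and 0.7. At 10% and r = 0.7 it is still 90%. The total of 768 stands, and the comparison at 10 cm is untouched by this problem.

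**What to change.** **Text.** Reconcile the Abstract, Outcome measures and the cortisol assessment section to one sampling window, the same in both arms. State that the first sample is drawn after randomisation and before the first ball positioning. The investigators must set that window so that it is consistent with the stated start of ball use.

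**Data.** Record the clock time and dilatation at the draw, and the clock time of first ball use.

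**Women already enrolled.** The Discussion reports 550 randomised, although its per-arm counts (225 + 225) add to 450. Where records allow, report how many first samples followed ball use. Keep all women in the analysis. Do not drop flagged first samples: they can occur only in the intervention arm, so dropping them would remove data from one arm and cut against the stated intention-to-treat approach.

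**Analysis.** Make the between-arm comparison of the 10 cm values, in all women with that sample, either the primary cortisol analysis or a pre-specified sensitivity analysis, and fix that choice before outcomes are compared by arm.

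**Cost.** A wording amendment, three recorded items and a records check. No extra blood sample is needed. If draw and ball-use times were not recorded, the check on past samples will be incomplete and should be reported as such.
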